## Abstract

**Background:**

The thyroid gland is an endocrine gland that has an impact on the body’s general metabolism. Thus, the secretions of the thyroid gland can modify the overall metabolism of the entire body. The prevalence of hypothyroidism is increasing quickly, with rates of 2%-5% in affluent countries and 11% in India. Individuals diagnosed with hypothyroidism need to take medication for the rest of their lives, resulting in significant stress. Therefore, conducting a study in this area is imperative.

**Objective:**

This study aims to assess the effectiveness of the therapeutic enema (Kshar Basti) and oral Kanchanar Guggul in the treatment of hypothyroidism.

**Methods:**

The trial group (n=45) will receive a therapeutic enema (Kshar Basti) followed by oral Ayurvedic drugs for 180 days. The control group (n=45) will be given levothyroxine tablets at a dosage of 1.6 µg/kg/day for the same duration. The objective is to examine the alterations in thyroid stimulating hormone (TSH) levels before and after the treatment.

**Results:**

Any deviation of the serum TSH by more than 20% from the initial values, while keeping triiodothyronine (T_3_), and thyroxine (T_4_) levels within the normal range, will be deemed statistically significant. Consequently, we anticipate a statistically significant variation in serum TSH levels between the therapeutic enema and Kanchanar Guggul treatments. Presently, the drug preparation operations are in progress. We expect to start enrolling patients in June 2024, do data analysis in December 2025, and acquire results by early 2026, marking the end of this trial.

**Conclusions:**

This study will evaluate the efficacy of the therapeutic enema, specifically Kshar Basti, in treating hypothyroidism. Furthermore, more research can determine the efficacy of a therapeutic enema (Kshar Basti) in treating overt hypothyroidism and hypothyroidism during pregnancy.

**Trial Registration:**

Clinical Trials Registry India CTRI/2023/05/052389; https://ctri.nic.in/Clinicaltrials/pmaindet2.php?EncHid=Nzk1NjY=&Enc=&userName=052389

**International Registered Report Identifier (IRRID):**

PRR1-10.2196/57287

## Introduction

### Overview

Thyroid hormones have various impacts on different biological systems. They play a crucial role in regulating many physiological processes, such as the vascular system, heart function, brain function (including cognition and mood), skeletal muscle, and bone health. Hypothyroidism refers to the inadequate production of thyroid gland secretions.

Hypothyroidism is primarily characterized by subclinical hypothyroidism (SCH), where levels of thyroid stimulating hormone (TSH) are elevated, but both free thyroxine (T_4_) and triiodothyronine (T_3_) levels remain within the normal range [1]. Overt hypothyroidism (OH) is the second kind of hypothyroidism, characterized by an increase in TSH, a drop in T_4_ and T_3_ levels, and the presence of clinical symptoms indicating hypothyroidism.

As per recommendations from endocrine societies, SCH is frequently managed with levothyroxine (L-thyroxine). This approach perhaps led to L-thyroxine becoming the most often prescribed medication in the United States starting in 2014, with over 15% of Americans aged 61 years and older using it. A recent extensive study conducted on older adults, known as the TRUST (Thyroid Hormone Replacement for Untreated Older Adults with Subclinical Hypothyroidism Trial), along with a subsequent thorough analysis of randomized controlled trials (RCTs), found no evidence of any advantages of L-thyroxine in terms of symptom relief or improvement in quality of life for patients with SCH [2]. Nevertheless, L-thyroxine is typically recommended indefinitely for SCH, which can be stressful for patients [3].

SCH is a burgeoning lifestyle-related ailment in India. In prosperous countries, the prevalence rate of hypothyroidism ranges from 2% to 5%. However, in India, the prevalence rate is 11% [4].

The prevalence rate of hypothyroidism increases with advanced age [5]. The American Thyroid Association guidelines advise the use of L-thyroxine in individuals with SCH and a TSH level of 10 mIU/L or higher. The supposition of SCH leading to OH is the basis of this statement [6].

There are 2 primary issues associated with L-thyroxine therapy, one of which is the uncertainty around the role of L-thyroxine in SCH. There are conflicting observations regarding it, and the patient must take L-thyroxine for the rest of their lives, which is distressing. Hence, there is an urgent requirement for Ayurvedic therapies in SCH.

Ayurveda is practiced in India, Nepal, and Sri Lanka, and is increasingly being adopted in Western countries. Modern medicine has demonstrated efficacy in managing acute medical emergencies, while Ayurveda may effectively handle chronic conditions that pose challenges for Western medical treatment. Individuals diagnosed with hypothyroidism frequently pursue Ayurvedic remedies [7].

Ayurveda recognizes a limited number of disorders that might be associated with hypothyroidism, and by applying Ayurvedic principles, it is possible to effectively manage this illness. Previous research [8] has examined the effectiveness of Ayurvedic treatment for hypothyroidism in multiple studies [9-11]. Nevertheless, these studies are subject to notable constraints, such as the lack of randomization, the absence of consistent therapy in the control group, a poor sample size, and insufficient follow-up time. We have chosen the following research to revise our protocol to overcome their limitations.

A recent study [10] demonstrated that administering Basti for a duration of 30 days, together with oral intake of 1 gram of Kanchanar Guggul twice a day with tepid water, and Vardhaman Pippali for 12 weeks, yielded better results compared to using only Kanchanar Guggul and Vardhaman Pippali in the same dosage for 12 weeks. However, the study conducted for only 12 weeks is inadequate to induce alterations in TSH concentration. Thus, we selected Kanchanar Guggul as the designated medication.

A study [12] indicated that a therapeutic decoction enema (Kshar Basti) was effective in treating hypothyroidism. A 10-day therapy regimen consisting of oral medications and therapeutic enemas using a decoction called Kshar Basti resulted in significant improvement in the symptoms of hypothyroidism. After 2 months of follow-up, the level of serum TSH decreased to 5.76 mIU/L, while T_3_ and T_4_ remained within the normal range. However, it is important to note that this study is limited to a single example.

### Objectives

#### Research Question

Can Ayurvedic treatments involving Kshar Basti (a therapeutic enema with herbal decoction) and oral administration of Kanchanar Guggul tablet effectively treat SCH?

#### Hypothesis

In SCH, the administration of Ayurvedic interventions, specifically Kshar Basti (decoction enema) followed by oral Kanchanar Guggul, has the potential to decrease elevated TSH levels while maintaining normal T_3_ and T_4_ levels.

#### Primary Objective

The main goal is to ascertain whether Ayurvedic therapy involves the administration of Kshar Basti, which is an herbal decoction enema, followed by an oral tablet. Kanchanar Guggul is efficacious in treating SCH.

#### Secondary Objective

Our secondary goal is to evaluate the appropriateness of Basti Karma (rectal enema therapy) and determine the dropout rate of the Basti course.

## Methods

### Overview

To assess and compare the effectiveness of the therapeutic decoction enema (Kshar Basti) and Kanchanar Guggul with L-thyroxine in the treatment of hypothyroidism, we will administer the therapeutic enema (Kshar Basti) for 24 days, followed by oral intake of Kanchanar Guggul for 153 days (a total of 180 days) in the study group. In the control group, L-thyroxine tablets will be taken for 180 days. The results will then be evaluated.

### Ethical Considerations

This study plan was presented to the Institutional Ethical Committee (IEC) of Mahatma Gandhi Ayurved College, Hospital, and Research Centre, and approval from the IEC has been obtained (Ref. MGACHRC/IEC/May-2022/479, dated May 23, 2022).

The participants of SCH will be informed regarding the ayurvedic procedures and the medications, and their written consent will be obtained on an informed consent form that is prepared in English and Marathi.

Periodically, participants will be required to provide their consent for panchakarma treatments and the collection of blood samples.

### Study Setting

This is a single-blind, RCT that aims to determine the superiority of one treatment over another (Figure 1). The study consists of 2 arms and follows a prospective design. Participants will be randomly assigned to either arm in a 1:1 ratio.

The study will be carried out in the Panchakarma department of the hospital affiliated with Mahatma Gandhi Ayurvedic College, hospital, and Research Center (Salod, Wardha district, Maharashtra, India). This study will be conducted following SPIRIT standards for RCTs (Figure 2).

**Figure 1 figure1:**
[figure not shown]
Study design. DM: diabetes mellitus; HTN: hypertension; TSH: thyroid stimulating hormone.

**Figure 2 figure2:**
[figure not shown]
SPIRIT (Standard Protocol Items: Recommendations for Interventional Trials) flowchart.

### Diagnostic Criteria

The diagnosis of SCH will be made per the *ICD-10* (*International Statistical Classification of Diseases, Tenth Revision*) criteria (SCH) as follows: TSH>4.50 µIU/mL, fT4=0.8-1.8 ng/dL, fT3=1.4-4.4 Pg/mL [13] (Textbox 1).

Eligibility, exclusion, withdrawal, and adverse drug reaction criteria.
**Eligibility criteria:**
Age: 20-60 yearsSex: AnyKnown case, or newly diagnosed case of subclinical hypothyroidism
**Exclusion criteria:**
Overt hypothyroidismSubclinical hypothyroidism with Diabetic Mellitus, hypertension, pregnancy, and gynecological disordersHashimoto thyroiditisKshar Basti contra-indications
**Withdrawal criteria:**
The participant may be withdrawn from the trial if there is one of the following:Any adverse event and adverse drug reaction (ADR) occurrenceVoluntary withdrawal by the participantViolation of inclusion and exclusion criteriaThere is noncompliance with the treatment regimen (a minimum of 80% compliance is essential to continue in the study)
**ADR**
If an ADR occurs during the trial, the participant will be treated at the institute-attached hospital, and the investigators will cover the costs.
**Criteria for discontinuing from the trial**
If the participant breaks the sequence of panchakarma therapy and misses the oral therapy for ≥7 days, he/she will not be considered in the trial.

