##### Course Duration

Basti will be administered daily for 8 days; after that, the participant must follow the regimen for 16 days. The total duration of the course will be 27 days (including Deepan-Pachan for 3 days), and after this course, Kanchanar Guggul will be administered for 153 days. The duration of the therapy will be 180 days, and the follow-up period will be 180 days.

Both groups of patients are restricted from taking or consuming any medications, devices, or nonpharmacological treatments that have an impact on hypothyroidism.

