### Limitations

Our investigation has some limitations. To begin with, 90 samples is still a moderate amount. To account for this prevalence rate, a minimum of 300 samples would be adequate. The duration of treatment is extended. Consequently, a large dropout rate is possible. Hence, a practical sample size of 90 was selected.

The preventive effect of these Ayurvedic interventions on SCH cannot be determined through our research. To accomplish this, an additional observational study with a minimum 1-year follow-up period is required.

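### Randomised participants can be taken out of the trial, not only off treatment, for events after randomisation, and one mandatory rule can apply only to the Ayurvedic arm

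*Protocol article*

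**What the plan says.** The trial is a two-arm superiority RCT: "Participants will be randomly assigned to either arm in a 1:1 ratio" (Study Setting). Textbox 1 then sets two groups of rules.

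- **Withdrawal criteria.** "The participant may be withdrawn from the trial if there is one of the following". The list includes any adverse event or adverse drug reaction, with no threshold of severity or relatedness, and non-compliance, with the note that "a minimum of 80% compliance is essential to continue in the study".
- **Criteria for discontinuing from the trial.** This rule joins two conditions with *and*: the panchakarma sequence is broken, and oral treatment is also missed "for ≥7 days, he/she will not be considered in the trial".

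Under Course Duration, the Ayurvedic course is described as follows: "Basti will be administered daily for 8 days; after that, the participant must follow the regimen for 16 days". Kanchanar Guggul is then taken for 153 days. The control arm takes levothyroxine tablets for 180 days. TSH, T3 and T4 are measured on day 181 (Screening Investigations). The Secondary Objective is partly to "determine the dropout rate of the Basti course", and the Limitations section accepts the risk of loss: "Consequently, a large dropout rate is possible".

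**The concern.** Adverse events, poor compliance and a broken course all happen on treatment, so they come after randomisation and may depend on the arm and on how the participant is doing. The wording ends participation in the trial or study, not just use of the study treatment. If these people are not measured on day 181, the comparison is between those who tolerated and kept to each regimen, and randomisation no longer protects it. One of the rules cannot be met in the control arm at all, so the filter differs between arms by construction.

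The loss cannot be repaired later. An analysis plan that names an intention-to-treat population cannot recover blood samples that were never taken.

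**Working it through.** **1. Which rule applies to which arm, and with what force**

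| Rule | Force of the wording | Arms it can reach |
|---|---|---|
| Any adverse event or ADR | Discretionary (*may*) | Both |
| Compliance below 80% | Reads as mandatory (*essential*) | Both |
| Broken panchakarma sequence **and** at least 7 days of oral therapy missed | Mandatory (*will not*) | Group A only |

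The first sentence of the Interventions section swaps the arm labels, but Textbox 2 and the Discussion make clear that Group A receives the enema course and Group B levothyroxine. The third rule therefore cannot remove anyone from Group B.

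**2. The two adherence thresholds side by side**

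Oral therapy is taken here as the 153-day Kanchanar Guggul phase; the 3-day preparatory powder is too short to give seven missed days by itself.

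- Seven missed days: 7/153 = 4.6%, so about 95% oral compliance.
- 80% rule, Group A oral phase: 0.20 × 153 = 30.6, so about 30 missed days are tolerated.
- 80% rule, Group B: 0.20 × 180 = 36 missed days are tolerated.

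A Group A participant with a broken sequence can be removed at seven missed oral days, while a levothyroxine participant with up to 36 missed days stays.

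**3. What the plan's own numbers allow for loss**

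The article states 40 per group plus 5, giving 45 per group and 90 in total; the additions are correct. It gives no expected dropout rate. The 5 extra offset at most 5/45 = 11.1% loss, and extra numbers do not correct selection.

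**4. Illustration of size**

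The removal rates and their link to response are assumptions, because the documents give neither. Throughout there is no true difference and the test is two-sided at 0.05 (the article gives 0.05 but not the sidedness).

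*Scenario 1: 20% of Group A (9 of 45) and none of Group B removed; removal correlates ρ with poor TSH response.*

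- Mean shift on the removal variable when the lowest 20% are cut: φ(0.842)/0.8 = 0.350 SD.
- Shift in TSH response: 0.3 × 0.350 = 0.105 SD; 0.5 × 0.350 = 0.175 SD.
- Standard error with 36 v 45: √(1/36 + 1/45) = 0.224 SD.
- Standardised shift: 0.105/0.224 = 0.47; 0.175/0.224 = 0.78.
- Rejection rate, P(Z > 1.96 − shift) + P(Z < −1.96 − shift): 7.6% and 12.3%. Simulation of 40,000 trials gave about 7.6% and 12.5%, with biases of 0.10 and 0.17 SD.

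*Scenario 2: 20% of Group A and 5% of Group B removed (36 v 43); in both arms those removed do g = 0.5 to 1.0 SD worse than those retained.*

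- Net bias: (0.20 − 0.05) × g = 0.075 to 0.15 SD.
- Standard error: √(1/36 + 1/43) = 0.226 SD.
- Rejection rate by simulation of 40,000 trials: 6.3% to 9.9%.

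**The case against.** The strongest reply is that the rules are milder than they look and that the analysis may be settled elsewhere. Most of the first part is right, and it limits what can be said.

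- **Adverse events.** A reader might infer that any adverse event puts a participant out. The text says *may*, so this is discretionary. Discretion still allows selection by judgement.
- **Broken course.** A reader might infer that failing the enema course is enough. As written, seven or more missed days of oral therapy are also required.
- **Mainly the Ayurvedic arm.** This is certain only for the broken-sequence rule. Group A has the heavier regimen, so a larger effect of the other two rules there is plausible, but the article gives no adverse event or compliance rates by arm.
- **Conflicting thresholds.** A tighter limit for people who also broke the sequence can logically coexist with an 80% rule. The passages are not strictly incompatible, but together they treat the arms differently and need to be reconciled.
- **Secondary objective.** It is tempting to say that the dropout objective is defeated because those who fail the course are not considered. The Results overview plans to report the rate of dropout from the Kshar Basti course, and the Audit section plans to track loss and its causes. Only a clarifying sentence is needed.
- **Progression to overt disease.** Violation of eligibility criteria is also a withdrawal ground. Reading it to cover later progression to overt hypothyroidism is conjecture.
- **Unseen analysis plan.** Analysis populations are often left to the SAP, so the article's silence on them is not itself the fault. The fault is the stated rules, which end participation before the outcome is measured.

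**Conclusion.** The point holds as a defect in the stated rules: participants leave a randomised trial because of on-treatment events, one mandatory rule can act in one arm only, and no text secures their day-181 outcome or keeps them in the comparison.

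The consequence is a risk of bias that could favour the Ayurvedic arm. Neither its direction nor its size can be fixed from the documents. Under the assumptions shown, the false-positive rate would be about 8 to 12% (20% v 0% removed) or about 6 to 10% (20% v 5%, equally informative), against a nominal 5%. A much larger figure results if those removed are assumed to be exactly the worst TSH responders, but nothing in the article supports that assumption.

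**What to change.** 1. In Textbox 1, separate stopping study treatment from leaving the study. Decisions to stop treatment stay with the investigators.
2. Take the planned day-181 TSH, T3 and T4 sample from every randomised participant who has not withdrawn consent, whatever their adverse events, compliance or course completion.
3. State that the primary analysis includes all randomised participants in their assigned arm.
4. Use the 80% criterion, defined the same way in both arms, only to form a supportive per-protocol set.
5. Reconcile the 80% criterion with the seven-day rule. Which threshold is clinically right is for the sponsor.
6. State that participants covered by the broken-sequence rule still count in the Kshar Basti dropout rate.

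The cost is protocol wording, plus an already planned blood draw in people who have stopped treatment.

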### Grouping

The grouping of participants is done in a parallel design where Group A (the trial group) consists of 45 participants and Group B (the control group) consists of 45 participants.

### Randomization

We will apply random allocation to recruit the participants in the study. Computer-generated random numbers will be used.

### Blinding

The allocation will be researcher blind. A third person, such as a nurse or panchakarma therapist, will help to allocate the participant using computer-generated random numbers. Since this study is researcher-blind, a PhD guide will allocate and assign the participants.

### Screening Investigations

Serum TSH will be measured before and after the study. On the 181st day, serum TSH, T_3_, and T_4_ will be measured. The above findings will be compared to the baseline findings.

### Criteria of the Assessment or Outcome Variable

A variation of more than 20% of the baseline value of serum TSH with normal values of T_3_ and T_4_ will be considered to determine the efficacy of the intervention. Therefore, decreasing serum TSH with no change in T_3_ and T_4_ means, Kshar Basti with Kanchanar Guggul is efficacious in SCH.

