### Evaluation Outcomes

The primary assessment result of our study is the disparity in the TSH, T3, and T4 levels compared to the initial values. We will deem any deviation of 20% or more from the baseline as statistically significant.

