## Discussion

### Principal Findings

The 45 participants in the control group will receive oral L-thyroxine. On the other hand, the trial group, also consisting of 45 participants, will get a treatment involving Kshar Basti and oral Kanchnar Guggul tablets. Both groups will undergo treatment for 180 days, and on day 181, we will assess the levels of TSH, T3, and T4 in the blood. We will compare the changes before and after therapy. We expect that the Ayurvedic intervention, specifically the combination of Kshar Basti and Kanchnar Guggul, will demonstrate statistically significant outcomes compared to the standard treatment. This would establish Ayurvedic intervention as a viable treatment option for SCH, eliminating the need for lifelong consumption of L-thyroxine tablets by the patient.

Hashimoto thyroiditis typically correlates with hypothyroidism. The thyroid gland produces numerous growth and vasoactive substances. The epithelial cells of the thyroid gland contain the glycoprotein known as vascular endothelial growth factor. It plays a critical role in the elevated levels of TSH in SCH.

A study compared the administration of Nigella sativa powder at a dosage of 2 grams per day for 8 weeks with the administration of placebos consisting of starches at the same dosage and duration. This RCT involved 47 human participants diagnosed with Hashimoto thyroiditis. Nigella sativa treated 23 of them, while starches served as a placebo for the remaining 24. The study determined that Nigella sativa seeds were useful in alleviating Hashimoto thyroiditis. It also successfully reduced vascular endothelial growth factor levels and body weight.

In Ayurveda, Nigella sativa is referred to as “Krishnajeeraka.” In our study, we will be administering Shivakshar Pachak Churna as “Deepan-Pachan” for the first 3 days. Nigella sativa is a constituent of Shivakshar Pachak Churna [16].

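### The 20% TSH efficacy rule is not tied to the protocol's own disease limit and has no lower bound, so meeting it cannot support the planned claim that the therapy treats SCH or makes L-thyroxine unnecessary

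*Protocol article*

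**What the plan says.** Under Criteria of the Assessment or Outcome Variable, the protocol article bases efficacy on "A variation of more than 20% of the baseline value of serum TSH", provided T3 and T4 are normal. The next sentence gives a direction but no amount: "decreasing serum TSH with no change in T_3_ and T_4_ means, Kshar Basti with Kanchanar Guggul is efficacious in SCH". The abstract ("Any deviation of the serum TSH by more than 20% from the initial values") and Evaluation Outcomes ("We will deem any deviation of 20% or more from the baseline as statistically significant") repeat a 20% figure without direction.

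Diagnostic Criteria defines SCH as TSH above 4.50 µIU/mL with fT4 of 0.8 to 1.8 ng/dL and fT3 of 1.4 to 4.4 pg/mL. The eligibility list admits known or new SCH and shows no upper limit for baseline TSH.

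Study Setting says that the trial "aims to determine the superiority of one treatment over another". Statistical Analysis plans a t test or a z-test. Principal Findings expects the result to establish the therapy as an option for SCH, "eliminating the need for lifelong consumption of L-thyroxine tablets by the patient". Principal Results expects it to show effective treatment of hypothyroidism.

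**The concern.** The disease is defined by an absolute TSH limit, but efficacy is judged by a relative change. No section requires TSH to return below 4.50 or says how low it may go. A result can therefore satisfy the efficacy rule while TSH remains in the range that defines the disease.

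The T3 and T4 condition looks like a safeguard but cannot act as one here. Participants with SCH have these hormones in range by definition, so a participant whose SCH persists passes the condition as easily as one whose SCH has resolved.

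What is at stake is the conclusion. Saying that a therapy treats SCH, or that patients no longer need L-thyroxine, requires evidence that the condition has resolved. A fall of just over 20% does not provide that. The article's own supporting case shows the gap: the Introduction cites it as evidence of effectiveness, yet after therapy "the level of serum TSH decreased to 5.76 mIU/L", which is still above 4.50.

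**Working it through.** **Inputs, all from the protocol article**

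- Efficacy cut-off: a change of more than 20% from baseline TSH, read here in its most favourable form as a fall (Criteria of the Assessment or Outcome Variable).
- Disease limit: TSH above 4.50 µIU/mL (Diagnostic Criteria). This unit equals mIU/L numerically.
- Lower TSH limit: none given.
- Assessment: day 181 against baseline (Screening Investigations).

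Both limits are stated rather than derived, so there is no plan figure to reproduce. The point does not depend on the sample size.

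**Step 1: where the two limits meet.** The rule is met when final TSH is below 0.80 × baseline. SCH persists when final TSH is above 4.50. They coincide when 0.80 × baseline = 4.50, so baseline = 4.50/0.80 = 5.625.

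**Step 2: either side of that point.** The fall needed to reach 4.50 is 1 − 4.50/baseline.

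| Baseline TSH | 0.80 × baseline | Fall needed to reach 4.50 |
|---|---|---|
| 4.6 | 3.68 | 2.2% |
| 5.0 | 4.00 | 10.0% |
| 5.5 | 4.40 | 18.2% |
| 5.625 | 4.50 | 20.0% |
| 6 | 4.80 | 25.0% |
| 7 | 5.60 | 35.7% |
| 10 | 8.00 | 55.0% |
| 20 | 16.00 | 77.5% |

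- Above 5.625: 12 to 9.5 is (12 − 9.5)/12 = 20.8%. It meets the rule at more than twice the disease limit. From 10, every value from 4.51 to 7.99 meets the rule and is still SCH.
- Between 4.50 and 5.625: 5.2 to 4.4 is (5.2 − 4.4)/5.2 = 15.4%. TSH normalises and the rule is not met.
- Lower end: with no floor, any fall up to almost 100% meets the rule if T3 and T4 stay in range.

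**Step 3: group means.** The same arithmetic applies to means. An arm whose mean goes from 7.0 to just under 5.6 meets the rule with its mean still above 4.50.

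**Step 4: the cited case.** A final value of 5.76 meets the rule from any baseline above 5.76/0.80 = 7.2. The article does not give that patient's baseline.

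**Step 5: how often, as illustration only.** The documents give no baseline distribution, so three were assumed: uniform 4.5 to 10, uniform 4.5 to 20, and 4.5 plus an exponential with mean 2. The SD of the log ratio of final to baseline TSH was set at 0.2 or 0.4.

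| Assumed median fall | Of those with a fall above 20%, TSH still above 4.50 | Of those who normalise, rule not met |
|---|---|---|
| 0 to 10% | 28 to 89% | 9 to 50% |
| 20 to 30% | 22 to 86% | 4 to 23% |
| 50% | 13 to 70% | 0.2 to 2.5% |

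The ranges are too wide to serve as an estimate.

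**The case against.** The strongest reply is that the rule fits the stated hypothesis, which asks only whether therapy can lower raised TSH while T3 and T4 stay normal. Relative change against normalisation is then a choice of endpoint. That stands as a defence of TSH change as the primary measure. It does not defend the claims in Principal Findings and Principal Results, which go beyond a reduction in TSH.

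A second reply is that, under a superiority aim, the Ayurvedic arm must still lower TSH more than L-thyroxine does. That limits the harm for the between-arm comparison. The second sentence of the efficacy rule, however, declares efficacy from a decrease in the Kshar Basti arm alone.

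Three stronger readings are tempting, and the document does not support them:

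- *Participants will be wrongly counted as successes or failures.* No section defines a responder or plans to compare proportions, and the planned tests point to mean change. The individual examples show what the rule permits, not a planned tally.
- *Superiority could be won by suppressing TSH.* The absence of a floor is plain, but no lower TSH limit is given and nothing suggests that the regimen suppresses TSH. The one post-treatment figure, 5.76, lies above 4.50. Nor does the article say whether the L-thyroxine dose is adjusted, so nothing can be built on its being fixed.
- *Normalisation must replace the primary endpoint.* From a baseline of 4.6, a 2.2% fall would then count. Because entry is selected on TSH above 4.50, such crossings can occur by fluctuation in either arm. A yes/no primary would also need a different test and a new sample size, and no response rates are given to derive one.

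The wording on unchanged T3 and T4 is a minor looseness. The sentence before it, the abstract and the hypothesis all speak of normal values.

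**Conclusion.** The concern holds in limited form and should be fixed. The efficacy rule is not anchored to the protocol's own limit of 4.50 and has no lower bound. Above a baseline of 5.625 it can be met while SCH persists, and between 4.50 and 5.625 TSH can normalise without meeting it. This needs only the two stated figures and is the same per participant or on means. Meeting the rule therefore cannot by itself support the claims of effective treatment or of no further need for L-thyroxine.

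The frequency is unknown. The conclusion rests on two assumptions: that T3 and T4 in the outcome section are the free hormones of Diagnostic Criteria, and that no part not shown, such as the study design figure, caps baseline TSH. A cap would remove the first mismatch only at or below 5.625, and the second would remain.

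**What to change.** 1. Stop using the 20% cut-off as proof of efficacy. Keep the between-arm comparison of TSH change from baseline as the primary analysis.
2. Add a key secondary outcome: the proportion in each arm with day-181 TSH at or below 4.50 and not below the laboratory's lower limit, with fT4 and fT3 within the ranges in Diagnostic Criteria.
3. Make any claim that the therapy treats SCH or replaces L-thyroxine conditional on that outcome. Otherwise limit the conclusion to a reduction in TSH.
4. Replace the wording on unchanged T3 and T4 with a requirement that both are within range.

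The cost is one more analysis of samples already planned and possibly a narrower conclusion. Power for the proportion is limited. With 45 per arm, no dropout and assumed proportions near one half, the 95% half-width for the difference is 1.96 × √(0.5 × 0.5 × 2/45) = 0.207, about 21 percentage points. That is a further reason for keeping the continuous change as primary.

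### The efficacy criterion is inconsistently fixed: the 20% change in TSH has no direction, the statements of direction have no size, and the 20% change is called statistical significance

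*Protocol article*

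**What the plan says.** The 20% figure appears in three places of the protocol article.

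- Abstract, Results: "Any deviation of the serum TSH by more than 20% from the initial values", with T3 and T4 kept in the normal range, is to be treated as statistically significant.
- Methods, Criteria of the Assessment or Outcome Variable, first sentence: "A variation of more than 20% of the baseline value of serum TSH", with T3 and T4 at normal values, is what efficacy is to be determined by.
- Results, Evaluation Outcomes: "We will deem any deviation of 20% or more from the baseline as statistically significant". The sentence before it names TSH, T3 and T4 together.

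A direction appears in two places.

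- Objectives, Hypothesis: the treatment "has the potential to decrease elevated TSH levels while maintaining normal T_3_ and T_4_ levels".
- Criteria of the Assessment or Outcome Variable, second sentence: "Therefore, decreasing serum TSH with no change in T_3_ and T_4_ means, Kshar Basti with Kanchanar Guggul is efficacious in SCH".

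Statistical Analysis specifies a Student t test, or a z-test if the data are not normal, with significance at P<.05. Study Setting calls the trial a superiority trial. Diagnostic Criteria require TSH above 4.50 µIU/mL at entry, and Screening Investigations place the final measurement on day 181.

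**The concern.** Participants enter because their TSH is too high, so a further rise is worsening. A threshold on change in either direction does not separate benefit from harm, and a statement that any decrease shows efficacy does not separate a relevant fall from measurement noise. The article never joins the two into a fall of more than 20%.

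This is the stated standard for judging whether the treatment works. If it stays as written, whoever analyses the data can choose between the readings after seeing the results. Calling a percentage change statistically significant adds a second problem: it offers a route to a claim of significance that bypasses the test the article specifies.

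**Working it through.** **1. The statements side by side**

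| Place | Direction | Size | T3/T4 condition | What it is called |
|---|---|---|---|---|
| Abstract, Results | none | above 20% | normal range | statistically significant |
| Outcome criterion, sentence 1 | none | above 20% | normal values | basis for efficacy |
| Outcome criterion, sentence 2 | fall | none | no change | efficacious |
| Evaluation Outcomes | none | 20% or above | none stated | statistically significant |
| Hypothesis | fall | none | remain normal | hypothesis |

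No row has both a direction and a size. The rows also differ on whether exactly 20% counts, and on whether T3 and T4 must be normal or unchanged. The last two conditions differ in substance: T4 can move within its range and stay normal.

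**2. Literal application**

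Take a baseline TSH of 10. A 21% rise gives 10 × 1.21 = 12.1, which meets the first sentence of the criterion if T3 and T4 are normal. A 1% fall gives 10 × 0.99 = 9.9, which meets the second sentence if T3 and T4 are unchanged.

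**3. Illustration of size**

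The article gives no figure to reproduce for this criterion and no within-person TSH variability. The coefficient of variation (CV) of a single measurement is therefore assumed. TSH is taken as log-normal with no true change, and the T3/T4 condition is ignored.

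- SD of the log ratio: s = √(2·ln(1+CV²)). At CV 20%, s = √(2·ln 1.04) = 0.280.
- P(rise above 20%) = 1 − Φ(ln 1.2 / s). At CV 20%, 1 − Φ(0.651) = 0.258.
- P(fall above 20%) = Φ(ln 0.8 / s). At CV 20%, Φ(−0.797) = 0.213.

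| Assumed CV | Rise >20% | Fall >20% | Either |
|---|---|---|---|
| 10% | 9.8% | 5.7% | 15.5% |
| 15% | 19.4% | 14.5% | 33.9% |
| 20% | 25.8% | 21.3% | 47.0% |
| 25% | 30.0% | 26.1% | 56.1% |

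Any fall at all has probability 50% whatever the CV.

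Selecting on a baseline above 4.50 lowers the share of rises through regression to the mean. With an assumed true median of 5.5 and log-SD of 0.35, simulation gives rises above 20% in 8%, 15%, 20% and 22% at the four CVs, and any fall in 54%, 56%, 57% and 59%.

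**The case against.** The strongest reply is that nobody could mistake the intention. The Hypothesis speaks of lowering a raised TSH, and the second sentence of the criterion opens "Therefore, decreasing serum TSH with no change in", which ties the direction to the sentence before it. On that reading the first sentence names the quantity to be examined and the second says which way is good. This stands as to intention: a reader might infer that the authors mean to count a rise as success, and the article does not support that.

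A second reply also stands. A reader might infer that worsened participants will be scored as responders, which would inflate response in both arms and blur the difference between them. The article describes no responder count. Evaluation Outcomes makes the primary result the change in hormone levels from baseline, and Statistical Analysis tests it by t or z. A comparison of means keeps its sign, so an arm whose TSH rises will show a rise.

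Third, the Discussion (Principal Findings) expects that the Ayurvedic treatment "will demonstrate statistically significant outcomes compared to the standard treatment". A reader might take this as a decision rule without direction. It is a stated expectation, and in context it means a favourable result.

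These replies do not repair the criterion. Knowing that a fall is meant still leaves open whether it must exceed 20%. The Abstract and Evaluation Outcomes say any deviation and supply no direction of their own. Nor does the specified test make the 20% rule harmless, because those same two places present the 20% change as statistical significance in its own right.

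**Conclusion.** The criterion is wrongly fixed as written and should be corrected before the data are analysed. This rests on the wording alone: three statements of size without direction, two of direction without size, two conditions on T3 and T4, two versions of the boundary at 20%, and a percentage change called statistically significant although significance is set at P<.05 elsewhere.

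The numerical size is illustrative. With no true effect, about 8-10% of participants would qualify by rising at an assumed CV of 10%, and 15-30% at assumed CVs of 15-25%. The lower figures include the assumed entry selection; the higher do not. These shares matter only if participants are classified individually, and the absence of any effect is not realistic for an arm given levothyroxine for 180 days. The conclusion does not depend on them.

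**What to change.** Use one criterion in the Abstract, the outcome criterion and Evaluation Outcomes: a fall in serum TSH of more than 20% from baseline at day 181, with T3 and T4 within the reference ranges listed under Diagnostic Criteria. Those ranges are written for the free hormones, so the criterion should name the same assays. State that rises and smaller falls do not meet it.

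Call this a threshold of relevance and remove the words on statistical significance from it. Let the efficacy claim rest on the between-arm test of TSH at P<.05, in favour of the Ayurvedic arm. If participants are also classified by the criterion, report the proportion by arm as supportive. The primary comparison need not become a dichotomised endpoint, and the shown sample size section gives no link between N and the 20% figure.

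The cost is small: wording changes, and an apparent response that may look less favourable than under the looser readings.
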